#### Secondary analysis

To identify any longer term effects, a repeated measures mixed model analysis of the primary outcome will be undertaken, comparing groups across all time points. The analysis will include adjustment for care home (as a random factor), baseline Barthel index score, and stratification factors: centre and type of care home. Similar analyses will be performed for mobility, mood and quality of life.

The number of falls will be compared using a Poisson or negative binomial model, with adjustments for care home, centre and type of care home as previously described. A sensitivity analysis of the outcomes will be performed to examine the potential effect of missing data. This will include best case, worst case and multiple imputation methods.

Analysis will be by intention to treat, whereby residents will be analysed according to the intervention to which they are randomised, regardless of whether they comply with the treatment. All participants irrespective of when they die, withdraw or are lost will be included in the arm to which they were randomised, including those that die after consent but prior to randomisation. Those participants that move home will be analysed by the home they were originally randomised to. Analyses will be performed using Stata (StataCorp,. Texas, USA) and SAS software (SAS Institute Inc., Cary, NC).

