### Randomisation

Homes and participants will be recruited and consented into the study before the randomisation process commences to reduce bias [17,18]. Homes will be stratified by residential care homes providing personal care and homes providing additional nursing care. Once the study co-ordinator ([name]) receives confirmation from the assessors that all residents in a participating home have given their consent and completed a baseline assessment, the homes will be grouped and randomised (50:50) to receive either the OT intervention or control (usual care). The assignment of cluster to either the OT intervention or control arm of the study will be conducted by the study co-ordinator. They contact the managers of the homes directly and make arrangements for the occupational therapist to visit the care home to commence the intervention. The allocation sequence will be generated by a statistician ([name]) using blocked randomisation within strata (centre and type of home; residential, nursing) at the Primary Care Clinical Research and Trials Unit at the University of Birmingham, independent from the research team. The details of the sequence will be unknown to any of the assessors or to the study co-ordinator. Allocation will be concealed from the independent assessors, but it is not possible to mask the treating therapists or residents from the intervention. The success of blinding will be evaluated at each follow-up stage by asking the assessors to record if the allocation has been revealed to them.

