#### Primary analysis

The primary outcome is the mean Barthel index score at the 3 month follow-up. A mixed model analysis will be used to compare Barthel index scores between the intervention and control groups. The primary analysis will be adjusted by care home (as a random factor), baseline Barthel index score, and stratification factors: centre and type of care home (nursing, residential). Participants that die before their follow-up date will be given a Barthel index score of zero at all subsequent follow-ups. In addition, participants will be categorised into 3 outcome groups based on an individual’s change in Barthel index score at 3 months from baseline (below 0 or death = ‘poor’, 0 to 1=’moderate’, 2 and above=’good’). A non-linear mixed effects model will be used to compare this ordinal outcome between the groups. Adjustments will be made for care home (random), centre and type of care home (fixed).

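### Residents who die between consent and their home's randomisation enter the primary comparison with a Barthel score of zero, which modestly dilutes the estimated effect

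*Protocol article*

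**What the plan says.** Three parts of the protocol article combine.

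- **Randomisation.** Consent comes first: "Homes and participants will be recruited and consented into the study before the randomisation process commences to reduce bias". A home becomes eligible for allocation only once it is confirmed that "all residents in a participating home have given their consent and completed a baseline assessment, the homes will be grouped and randomised". There is thus a gap between a resident's consent and the home's allocation. Its length is not given.
- **Secondary analysis, intention-to-treat paragraph.** The general rule reads: "All participants irrespective of when they die, withdraw or are lost will be included in the arm to which they were randomised". The sentence then extends the rule expressly to deaths in the gap before allocation: "including those that die after consent but prior to randomisation". The paragraph stands under the secondary analysis heading, but it is worded for the trial's analyses as a whole.
- **Primary analysis.** "The primary outcome is the mean Barthel index score at the 3 month follow-up". On deaths: "Participants that die before their follow-up date will be given a Barthel index score of zero at all subsequent follow-ups". In the ordinal version of the outcome, death falls in the worst category. Neither rule is limited to deaths after randomisation.

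**The concern.** The same paragraph defines intention to treat as analysing residents by the intervention to which they are randomised. A resident who died before the home was allocated had an outcome already fixed at that point and could receive neither arm's care. For that resident the treatment effect is zero by construction.

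Read together, the rules place such residents in the primary comparison at zero. This has two consequences. The expected difference is pulled towards zero in proportion to their share. Each of them also lies far below the living residents' scores, which adds variance unrelated to treatment. Including them protects nothing, because membership of this group is settled before allocation.

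**Working it through.** **Inputs from the Sample size section:** difference 2 points, SD 3.7 (variance 13.69), ICC 0.4, 90% power, 5% significance (taken as two-sided), 10 residents per home, 26% attrition, 33 homes per arm before attrition and 45 after.

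**The plan's own figure reproduces.** Per arm without clustering: 2 × [3.7 × (1.960 + 1.282) / 2]² = 71.9. The design effect is 1 + 9 × 0.4 = 4.6. The product is 330.8, against 330 stated. Allowing for attrition, 330 / 0.74 = 446, or 45 homes of 10 per arm.

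**Assumptions, because the document gives neither figure:** f, the share of analysed residents who died between consent and randomisation, is 2% or 4%. b, the mean Barthel score of the other residents, is 8 (range 6 to 10). The share f is the same in every home.

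**Formulas**

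- Expected difference = 2 × (1 − f)
- Total variance = (1 − f) × 13.69 + f(1 − f) × b²
- Between-home variance = (1 − f)² × 0.4 × 13.69 = (1 − f)² × 5.476
- Within-home variance = total − between
- Variance of an arm mean = between / 45 + within / (45 × 7.4), where 7.4 = 10 × 0.74 and 45 × 7.4 = 333
- SE of the difference = √(2 × variance of an arm mean)
- Power = Φ(difference / SE − 1.960)

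The between-home part is scaled by (1 − f)² because, with a common share of zeros in every home, differences between homes shrink. The extra variance then arises between individuals.

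**No such deaths (f = 0).** 5.476/45 + 8.214/333 = 0.1464; SE 0.541; 2/0.541 = 3.697; power 95.9%.

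**f = 4%, b = 8.** Total variance is 0.96 × 13.69 + 0.04 × 0.96 × 64 = 13.14 + 2.46 = 15.60 (SD 3.95). Between homes: 0.9216 × 5.476 = 5.047. Within homes: 10.553. Variance of an arm mean: 5.047/45 + 10.553/333 = 0.1438. SE 0.536; 1.92/0.536 = 3.580; power 94.7%.

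| f | b | Expected difference | Total SD | Power, 45 × 7.4 per arm |
|---|---|---|---|---|
| 0 | – | 2.00 | 3.70 | 95.9% |
| 2% | 8 | 1.96 | 3.83 | 95.3% |
| 4% | 6 | 1.92 | 3.81 | 95.2% |
| 4% | 8 | 1.92 | 3.95 | 94.7% |
| 4% | 10 | 1.92 | 4.12 | 94.2% |

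At 33 homes of 10 per arm, without the attrition margin, the same method gives 89.9% with no such deaths, 89.2% at f = 2% and 88.4% at f = 4% (b = 8).

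**Excluding these residents.** At f = 4% the home size falls to 7.4 × 0.96 = 7.104. The variance of an arm mean is then 5.476/45 + 8.214/(45 × 7.104) = 0.1474, and power is 95.8%. The gain over keeping them is 95.8 − 94.7 = 1.1 points at b = 8.

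**The case against.** The strongest defence is that the rule is pre-specified, treats both arms alike, keeps the whole consented cohort of each randomised home and errs towards no difference. Such deaths precede allocation, so they are balanced in expectation and type I error is unaffected. Their number may be small: residents receiving end-of-life care (life expectancy under 6 months) are excluded. At 2–4% the shift is 0.04 to 0.08 points, against the 2 points that the protocol calls clinically meaningful. All of this stands, and it limits how serious the point is. It does not justify the rule. Leaving these residents out depends only on a fact fixed before allocation, so it cannot introduce selection bias, and every home stays in its arm.

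A reader might infer a larger loss of power by applying the design effect at ICC 0.4 to the whole inflated variance. That gives 91.4% at f = 4% and b = 8, and 89.0% at b = 10, below the planned 90%. The documents do not support this. It treats the added variance as clustered by home to the same degree as the Barthel score, whereas under a common share of deaths it lies between individuals and the ICC falls to about 5.047/15.60 = 0.32. The loss would be larger than tabulated if these deaths concentrated in particular homes, but nothing in the protocol indicates that.

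A reader might also count chance imbalance between arms in these deaths as a separate bias. It is sampling error, already included in the increased variance.

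**Conclusion.** The defect is real and follows from explicit text: residents dead before allocation are analysed at zero in the primary comparison and as poor in the ordinal one. The estimated difference is biased towards zero by 1% of its size for each 1% of such deaths; this part does not depend on the ICC or on b. Power falls by about 0.6 points at an assumed 2% (b = 8) and by 0.7 to 1.7 points at an assumed 4% (b = 6 to 10), and stays above 90% with 45 homes of 7.4 per arm.

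These sizes rest on assumed values of f and b, an equal share of deaths across homes, and the planned SD without any gain from baseline adjustment. It would go too far to conclude that the rule threatens the trial's conclusion or raises the risk of a false positive. Severity is minor to moderate.

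**What to change.** Define the primary analysis population as consented residents alive on the date their home was randomised. Apply the zero score, and the poor category for death, only to deaths after that date. Report earlier deaths by arm in the flow diagram. A sensitivity analysis may keep them in, scored as now.

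The cost is a sentence or two in the analysis section and a slightly smaller analysed number. The cut must be made strictly by date, so date of death and date of the home's randomisation are needed for every resident who dies. The article does not say that both are recorded, so this should be confirmed.

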#### Health economic evaluation

Outcomes from health economic evaluation analyses will establish cost effectiveness of a treatment expressed as incremental cost per quality-adjusted life-years (QALYs) gained. Generalised linear models will be used to investigate differences between interventions for QALYs and costs. Bootstrap methods will be adopted to produce incremental cost effectiveness ratio and associated confidence intervals. Cost-effectiveness acceptability curves will be generated to reflect the probability that a treatment will be cost effective given a society’s willingness to pay in terms of price per QALY gained.

### Governance

#### Ethical approval

Favourable ethical opinion for this study was obtained from the National Research Ethics Service, Coventry Research Ethics Committee (Reference: 09/H1210/88). The study was granted an International Standard Randomised Controlled Trial Number (00757750).

#### Trial management

A trial steering group has been established to monitor the governance of the study consisting of the main research team, an independent chair, a geriatrician, an occupational therapist, a physiotherapist with expertise in rehabilitation research a patient representative, and a representative from the National Institute for Health Research. A data monitoring committee has been established with an independent geriatrician as chair, a statistician and an occupational therapist. During the development of this protocol, a patient representative was consulted.

#### Service user involvement

Service user (and carer) involvement will be incorporated at all levels of this study. Service user (and carer) involvement will not be a ‘stand-alone’ activity but rather an integral part of all aspects of this study. Service users (and carers) will be directly involved as research ‘partners’ and not just as ‘data providers’. All support for service users (and carers) involvement will be provided by the Stroke Research Network members who have expertise in training and supporting service users (and carers) for involvement in National Health Service research, service evaluation and development.

## Discussion

The methodological limitations and considerations of cluster randomised trials are well reported [34] and have been addressed in the current study protocol. Furthermore, the choice of clustering design to reduce intervention contamination was a key component of the development of this trial. Previous cluster randomised trials demonstrated that a relatively small level of OT may have detectable and relatively long-lasting effects on morbidity and possibly mortality in care homes residents with stroke-related disabilities [10,11]. These studies enrolled small numbers of clusters and participants and were conducted in specific areas of the UK, which reduces the generalisability of the findings to residents in care homes more widely. The current study will be the largest cluster randomised control trial of OT in care homes to date. It will provide clinically relevant information on the effect of OT services on activities of daily life compared to usual care. Furthermore, it aims to establish the effects of OT services on aspects such as mobility, depression and quality of life, which are major challenges experienced by many residents [2]. Finally, this study will evaluate the health economic impact of OT services compared to usual care. In combination, the findings of this large scale cluster randomised controlled trial will assist in the formulation of UK guidelines and policies on the provision of OT services for residents with stroke-related disabilities in care homes.

## Abbreviations

OTCH, Occupational therapy in care homes; OT, Occupational therapy; UK, United Kingdom; QALY, Quality adjusted life years; ICC, Intra class correction; TIA, Transient ischaemic attack.

## Department of Health Disclaimer

The views and opinions expressed therein are those of the authors and do not necessarily reflect those of the Health Technology Assessment programme, National Institute for Health Research, National Health Service or the Department of Health.

